# INTRODUCTION

##

## Background

Chagas disease ranks among the main neglected tropical diseases (NTDs) in Latin America and the Caribbean [1]. *Trypanosoma cruzi*, its etiologic agent, induces heart and digestive disease and reduces life expectancy in approximately 30-40% of the infected people [2,3]. The parasite infects 6-9 million people, the majority of which primarily were rural residents living in poverty with little access to healthcare services [4]. A well-known hotspot of Chagas disease and other NTDs is the Gran Chaco ecoregion which mainly extends over sections of Argentina, Bolivia, and Paraguay [5].

The two drugs (nifurtimox and benznidazole) registered for treatment of human infection with *T. cruzi* since the late 1960s and early 1970s were shown to be especially effective in young age groups during the acute and early chronic phase regardless of transmission mode [3,6-10]. Both drugs may cause adverse drug-related reactions (ADR) of various types, frequency and severity [11-14]. Less than 1% of patients infected with *T. cruzi* have access to parasiticidal treatment [15]. The challenge of how to address diagnosis and treatment of *T. cruzi* infection in resource-poor, remote rural settings through primary health care has yet to be developed and program effectiveness documented to meet the challenge of treating the sizable population of infected rural residents and correct health inequities.

**OBJECTIVE**

To develop, implement and test a strategy based on strengthened primary healthcare attention and broad social participation with the goals of increasing access to diagnosis and treatment of human *T. cruzi* infection in sparsely populated rural sections of Pampa del Indio municipality.

# study design

## Study type

Non-randomized prospective study in children residing in a well-defined rural endemic area.

## Population

### Selection criteria

Children aged between 9 months and 18 years old resident of Pampa del Indio, (rural) Area I as defined in Gurevitz et al. 2011, who were seropositive for *T. cruzi*.

### Inclusion criteria

- Children of any gender or ethnic group, aged between 9 months and 18 years old, residents of Pampa del Indio Area I, seropositive for *T. cruzi* by at least two different techniques and eligible for treatment with benznidazole as per this treatment protocol.
  - Serodiagnostic criteria: At least 2 positive serological tests for *T. cruzi* infection using conventional (Chagatest, Wiener) and recombinant antigens (ELISA Rec V3.0, Wiener), and for serologically discordant sera indirect immunofluorescence antibody assay (Parasitest, Laboratorio IFI).
- Informed consent signed by the parent or guardian and consent of the patient. For community meetings including indigenous residents, explanations will be translated by an indigenous healthcare agent or by an appointed indigenous community member and consent will be obtained collectively and individually.

### Exclusion Criteria

- Pregnant or lactating women.
- Individuals with renal or hepatic dysfunction or psychiatric problems or with severe or generalized disease or immunocompromised.
- Patients who reportedly had been treated with benznidazole or nifurtimox before.

### Criteria for withdrawal from the study

- Severe adverse reaction potentially attributable to benznidazole or not.
- Any situation that may put the safety of the patient at risk, according to the judgment of attending physicians.

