## Follow up

Monitoring of medication adherence and ADRs will be conducted by local healthcare agents in five weekly appointments at the health post or at the patient’s home where they will record the patient’s body weight and temperature, and the number of benznidazole pills remaining. The patients’ parents or guardians will notify the healthcare agents the onset of any adverse drug-related reaction, sign or symptom, or may directly communicate with the coordination team by cell phone. The research team will keep a treatment diary to record the doses administered, its timing, and any symptoms or problems related to treatment.

All ADRs detected during drug administration (i.e., type, date of onset and remission, duration, and specific treatment indicated) will be recorded in each patient’s clinical history. Patients showing a severe or moderate, prolonged exanthema combined with fever will be transported to the local hospital for medical evaluation. Temporary suspension or benznidazole dose reduction or treatment with corticoesteroids or antihistamines may be prescribed to patients with mild or moderate reactions. Healthcare agents will follow up the evolution of ambulatory patients until remission.

The local physicians will re-evaluate the patients’ clinical status at the healthcare posts or schools 10, 20-30 and 60 dpt, and add these results to each individual clinical history. Each clinical evaluation will include a semiologic exam and clinical laboratory tests at 20-30 and 60 dpt to assess the same variables as determined at baseline. A blood sample aliquot will be kept for serological and molecular diagnosis as described above. Additional blood samples will be collected at 180 dpt for serological and molecular diagnosis of *T. cruzi* infection. All sera collected at 0, 60 and 180 dpt will be tested in parallel to assess any decay in specific antibody titers relative to baseline values.

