# Data Analysis and statistical methods

Treatment-related primary outcomes included treatment coverage (i.e., percentage of seropositive patients up to 18 years of age at serodiagnosis that were treated with benznidazole relative to the number of seropositive patients in this age group who were eligible for treatment); treatment quality (based on individual completion, medication adherence – as determined by the average percentage of benznidazole pills taken relative to those provided for each specific time period- and ADR management --percentage of patients who presented ≥1 ADR and were able to complete treatment), and therapeutic response (detection of *T. cruzi* DNA by kPCR and qPCR in patients who completed the full treatment course and had ≥80% of medication adherence). Patients with three or fewer pill counts and those withdrawn from or who abandon treatment will be excluded from adherence estimates. The therapeutic response to treatment will be essentially measured by the proportion of patients who were qPCR-negative at 180 dpt among those who had been qPCR-positive before treatment.

Statistical analysis will include Friedman’s two-way non-parametric analysis of variance for testing differences among repeated measurements of biochemical variables before treatment and at 20 and 60 dpt; Kendall’s *K* as an index of concordance; Fisher’s exact test or χ^2^ tests for investigating two by two contingency tables of independent data, and exact McNemar significance probabilities for paired data with small cell frequencies. The nominal level of statistical significance is set at a *P* value of 0.05. All tests will be performed using Stata 12.

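### The protocol does not separate stopping benznidazole from leaving the study, so later laboratory, serology and PCR data on children with severe reactions are not secured

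*Protocol*

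**What the plan says.** The Population part of the protocol has a short section headed "Criteria for withdrawal from the study". It gives two grounds. The first is "Severe adverse reaction potentially attributable to benznidazole or not". The second is "Any situation that may put the safety of the patient at risk, according to the judgment of attending physicians".

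The Follow up section plans clinical re-evaluation at 10, 20-30 and 60 dpt, with laboratory tests at the last two and a blood aliquot kept for serology and PCR. It then adds: "Additional blood samples will be collected at 180 dpt for serological and molecular diagnosis". On reactions it says "Temporary suspension or benznidazole dose reduction or treatment with corticoesteroids or antihistamines may be prescribed to patients with mild or moderate reactions", and on later contact "Healthcare agents will follow up the evolution of ambulatory patients until remission". It does not say whether a withdrawn child still attends the remaining visits.

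The section on data analysis and statistical methods uses a different term: "those withdrawn from or who abandon treatment will be excluded from adherence estimates". It limits therapeutic response to children who finished the course with at least 80% adherence, and measures it mainly by qPCR negativity at 180 dpt among those qPCR-positive at baseline. It plans a Friedman test of biochemical variables before treatment and at 20 and 60 dpt.

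**The concern.** Stopping a drug and leaving a study are different events. A child can stop benznidazole and still give blood at 60 and 180 dpt. The protocol gives criteria only for leaving the study, and applies them to severe reactions whatever the cause. A field team following that text as written would have no reason to collect further scheduled samples.

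The trigger is tolerance, so the missing data would not be a random subset. Two things are at stake:

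- The biochemical comparison would lean towards children who tolerated treatment, when liver and blood values after a severe reaction are among the most useful safety data.
- Parasite DNA and antibody levels after a shortened course would not be observed. The stated objective is to test a strategy for access to diagnosis and treatment, so the outcome of every treated child is relevant to it.

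Who stays in follow-up is a conduct rule. A statistical analysis plan cannot recover a sample that was never drawn.

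**Working it through.** **No planned figure to reproduce.** The protocol states no sample size, expected response, severe-reaction rate or dropout rate. The check is therefore a reading of the sections side by side, followed by an illustration on assumed inputs.

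**Step 1: what withdrawal means.**

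- Withdrawal criteria: the heading refers to the study.
- Statistical section: the wording refers to treatment.
- Follow up: the sampling schedule is neither limited to children still on the drug nor expressly continued for those taken off it.

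The text allows two opposite practices. Under the literal reading of the criteria, sampling ends; under the statistical section's wording, it could go on.

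**Step 2: which outcomes depend on the reading.**

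| Outcome | Needs data after withdrawal? | Effect of the literal reading |
|---|---|---|
| Treatment coverage | No | None |
| Completion | No | None; the child counts as a non-completer |
| ADR management | No | None; the child counts as having an ADR without completing |
| Adherence | Not applicable | None; those withdrawn are excluded anyway |
| Therapeutic response (adherent completers) | Not applicable | None; a stopped child is outside the set, sampled or not |
| Biochemistry before, 20 and 60 dpt | Yes | A child lacking a later value falls out of a complete-block Friedman test |
| Serology at 60 and 180 dpt | Yes | Any later sample is missing |
| qPCR at 180 dpt, all treated (supplementary) | Yes | Not fully observed |

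The 60 dpt loss is not universal, because a severe reaction at the very end of the course may follow that sample. The 180 dpt sample would be lost in every case.

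**Step 3: illustration for the all-treated qPCR figure.** Let w be the share of treated, baseline-qPCR-positive children without a 180 dpt result, and R the proportion negative among those observed. Both are assumptions. The all-treated proportion lies between

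lower = (1 − w) × R (missing counted as failure), and

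upper = (1 − w) × R + w (missing counted as success).

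With R = 0.90:

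| w | lower | upper |
|---|---|---|
| 2% | 0.98 × 0.90 = 0.882 | 0.902 |
| 5% | 0.95 × 0.90 = 0.855 | 0.905 |
| 10% | 0.90 × 0.90 = 0.810 | 0.910 |
| 20% | 0.80 × 0.90 = 0.720 | 0.920 |

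The width, upper − lower, equals w for any R. That holds for any missing binary outcome and is no estimate for this trial. It shows that the cost is about proportional to the unknown withdrawal rate, and that bounds and a missing-as-failure analysis remain available.

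**The case against.** The strongest reply is that the loss is inferred. No section says that withdrawn children are not sampled, the Follow up schedule is not restricted to children on the drug, and the statistical section's own phrase suggests that withdrawal may mean stopping the drug. This stands as far as it goes: the loss follows from a heading and from silence. But a protocol that permits both practices on a point deciding whether blood is drawn needs correcting.

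A reader might also infer that no all-treated result can be computed. The document does not support that. Coverage, completion and ADR management need no later sample, and the all-treated qPCR figure can be bounded or run with missing as failure. Only a fully observed result is unsecured.

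Nor does the rule bias the planned response estimate. The restriction to adherent completers already excludes these children, whether or not they are sampled.

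It would also be wrong to say that nothing is recorded after a severe reaction. Follow up sends certain skin reactions with fever to hospital for evaluation, and has the type, timing, duration and treatment of each ADR entered in the clinical history. What it does not attach to withdrawn children is the scheduled laboratory, serology and PCR work.

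Finally, mild and moderate reactions may be handled within treatment, so the children affected may be few. That is a fair caution about size; the document gives no rate to settle it.

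**Conclusion.** The point holds in a limited form. The withdrawal criteria, the Follow up section and the statistical section do not agree on whether a child taken off benznidazole remains under observation. On the literal reading, scheduled laboratory, serology and PCR data after a severe reaction are lost in a way related to tolerance. The biochemical comparison then over-represents tolerant children, and the completer-only response has no fully observed all-treated result beside it.

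The size cannot be stated. The bounds above rest wholly on assumed values of w and R, and on the literal reading being the one applied. The change is worth making because it is cheap and the data cannot be recovered later; no planned primary estimate is shown to be wrong.

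**What to change.** Reconcile the three sections and leave the criteria themselves unchanged.

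1. In the withdrawal section, distinguish stopping benznidazole from leaving the study.
2. In Follow up, state that a child whose treatment is stopped is still invited to the remaining scheduled examinations, laboratory tests and 60 and 180 dpt samples, unless consent is withdrawn or the attending physician judges those procedures unsafe. The physician's safety ground for ending study procedures must be kept.
3. In the statistical section, report the available laboratory and 180 dpt PCR results of stopped children beside those of completers, with the number stopped and the number sampled.

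The cost is a short amendment and a few extra blood draws at visits already scheduled. Some families will decline them, so the all-treated picture may remain incomplete, but the remaining gap would be smaller and its size known.

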# research plan

## Study area

## The intervention will be conducted in Pampa del Indio (25°55’S 56°58’W), Chaco, Argentina. The study area (denominated Area 1) included 353 houses and a few public buildings grouped in 13 rural villages distributed over a 450 km^2^ section as described in Gurevitz et al. (2011). The study area was inhabited by 1,187 people in 2007. The only existing medical facility is a first-level public hospital with four physicians; the primary healthcare system had 5 posts distributed across the study area, and there were 8 primary schools.

All inhabited house compounds were sprayed with pyrethroid insecticides in November-December 2007. All houses found to be reinfested over 2008-10 were selectively re-sprayed with insecticides after each periodic survey. House infestation at the time of the planned human serosurveys (September 2010-March 2011) was <1% and mainly occurred in peridomestic structures; none of the bugs collected were infected with *T. cruzi* as determined by microscopic analysis of feces at 400×.

## General overview of the study

The study includes five successive phases: preparatory, participatory planning, capacity strengthening of local health personnel, diagnostic surveys, and treatment and follow-up, all of which were deemed to be completed within 1.5 years.

Preliminary meetings with local authorities, health personnel, rural school teachers, and community leaders will be conducted to inform them of the planned intervention program and request their feedback. Community workshops will be conducted to introduce the research team, communicate the program’s objectives and phases, identify local capacities and weaknesses linked to healthcare activities, and establish a permanent channel of communication with local referents. Householders of each target village within Area 1 of Pampa del Indio will be convened by radio broadcasts and written messages to schoolchildren’s parents at each rural school. Capacity strengthening of health personnel will be achieved over three meetings whose ultimate goal is to define more precisely the roles of rural healthcare agents and coordination team members, and to adapt field activities to the detected constraints.

## Diagnostic surveys

*Serosurveys.* Residents from all the study villages will be summoned to the nearest healthcare post or school for blood sample extraction. Blood samples will be drawn by venipuncture from all residents older than one year of age (3 mL from children aged 1-2 years old, and 5-7 mL from older patients), and capillary blood taken from infants aged 9-12 months by fingerprick or heal prick. Venipuncture is preferred to collecting whole blood on filter paper or using other methods because of the large seroprevalence of *T. cruzi* infection expected (30 to 50%); to minimize blood extraction rounds (which increase dropouts), and to provide conclusive serological results as early as possible and progress to the treatment phase. Diagnostic surveys and patient recruitment will be carried out by [name] and [name]. The diagnostic surveys will be conducted over 3-5 months at local schools or health posts.

Each serum will be tested for *T. cruzi* infection in duplicate by two ELISA tests using conventional (Chagatest, Wiener) and recombinant antigens (ELISA Rec V3.0, Wiener) according to manufacturer instructions, at the Laboratory of Eco-Epidemiology in Buenos Aires. Serologically discordant samples will be tested by an indirect immunofluorescence assay (Parasitest, Laboratorio IFI). Individuals positive by at least two different methods will be considered seropositive for *T. cruzi*. For external quality control, a random sample of 30 sera will be tested blindly at the Instituto Nacional de Parasitología Dr M. Fatala Chaben.

*Molecular diagnosis.* Detection of *T. cruzi* DNA will be conducted using a qualitative PCR assay targeted to the minicircles of the kinetoplast (kPCR) and by a quantitative PCR (qPCR) targeted to the nuclear satellite sequence [44,49]. For qPCR, samples will be run in duplicate using a commercial kit (SYBR GreenER qPCR SuperMix Universal, Invitrogen, Life Technologies, USA) at Instituto Nacional de Parasitología Dr. M. Fatala Chaben. Parasite DNA concentration will be expressed as equivalent amounts of parasite DNA per ml (Pe/mL).

## Patient recruitment

Patients found to be seropositive for *T. cruzi* and their parents or guardians will be summoned for a meeting conducted at the nearest rural school or healthcare post. Local physicians will communicate treatment benefits and eventual risks of ADRs to the patients. A locally adapted plan for monitoring ADR and medication adherence will be discussed and agreed upon.

Prior to the onset of treatment with benznidazole, the attending physicians will evaluate the patients’ clinical status at the healthcare posts or schools immediately before treatment (0 days posttreatment initiation, dpt) and record the results in an individual clinical history. Each clinical evaluation will include a semiologic exam, an electrocardiographic exam, and clinical laboratory tests to assess hematocrit and hemoglobin levels, platelets, white cell counts, alanine aminotransferase, aspartate aminotransferase and alkaline phosphatase, cholesterol, uremia, serum creatinine and serum proteins at the local hospital. Women in reproductive age will be tested for pregnancy. A blood sample aliquot will be kept for serological and molecular diagnosis as described above.

## Treatment

Benznidazole (Radanil^®^, Roche) will be provided free of charge by the National Chagas disease program, and administered in two daily doses (5-8 mg/kg-day) during 60 days over April-July 2011 by parents or guardians in an outpatient setting. Tablets will be fractioned by an hospital pharmacist to match individualized dosing regimens. Benznidazole doses and a weekly calendar will be provided to each patient, parent or guardian for each 15-day period to keep record of the doses taken daily and facilitate monitoring of medication adherence.

## Follow up

Monitoring of medication adherence and ADRs will be conducted by local healthcare agents in five weekly appointments at the health post or at the patient’s home where they will record the patient’s body weight and temperature, and the number of benznidazole pills remaining. The patients’ parents or guardians will notify the healthcare agents the onset of any adverse drug-related reaction, sign or symptom, or may directly communicate with the coordination team by cell phone. The research team will keep a treatment diary to record the doses administered, its timing, and any symptoms or problems related to treatment.

All ADRs detected during drug administration (i.e., type, date of onset and remission, duration, and specific treatment indicated) will be recorded in each patient’s clinical history. Patients showing a severe or moderate, prolonged exanthema combined with fever will be transported to the local hospital for medical evaluation. Temporary suspension or benznidazole dose reduction or treatment with corticoesteroids or antihistamines may be prescribed to patients with mild or moderate reactions. Healthcare agents will follow up the evolution of ambulatory patients until remission.

The local physicians will re-evaluate the patients’ clinical status at the healthcare posts or schools 10, 20-30 and 60 dpt, and add these results to each individual clinical history. Each clinical evaluation will include a semiologic exam and clinical laboratory tests at 20-30 and 60 dpt to assess the same variables as determined at baseline. A blood sample aliquot will be kept for serological and molecular diagnosis as described above. Additional blood samples will be collected at 180 dpt for serological and molecular diagnosis of *T. cruzi* infection. All sera collected at 0, 60 and 180 dpt will be tested in parallel to assess any decay in specific antibody titers relative to baseline values.

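### Pill counts are scheduled at five weekly visits in a 60-day course, so the adherence outcome and the 80% gate may leave up to about 25 days uncounted

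*Protocol*

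**What the plan says.** Under Treatment, benznidazole is given "during 60 days over April-July 2011 by parents or guardians in an outpatient setting". It is handed out with a calendar "for each 15-day period to keep record of the doses taken daily and facilitate monitoring of medication adherence", which makes four supplies in 60 days.

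Under Follow up, the pill count is assigned to the healthcare agents: "Monitoring of medication adherence and ADRs will be conducted by local healthcare agents in five weekly appointments". At these visits they record, among other things, "the number of benznidazole pills remaining". The first day of the visits is not stated. Physicians see the patients at 10, 20-30 and 60 days after treatment start, but what is listed for those visits is clinical examination and laboratory work, with no pill count. A second dose record is planned: "The research team will keep a treatment diary to record the doses administered, its timing, and any symptoms or problems related to treatment".

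Under Data Analysis and statistical methods, adherence is the "average percentage of benznidazole pills taken relative to those provided for each specific time period" and forms part of the primary outcome on treatment quality. "Patients with three or fewer pill counts" are left out of the adherence estimates, as are patients who are withdrawn or abandon treatment. Therapeutic response, also a primary outcome, is assessed in patients who completed the full course and "had ≥80% of medication adherence".

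**The concern.** The visit schedule, the length of the course and the adherence definition do not fit together. The minimum number of pill counts shows that the percentage is built on those counts, and four are enough. Five weekly counts do not span 60 days. The resupply step and the day-60 evaluation could have closed the gap, but no count is specified at either.

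Two primary outcomes are affected. If pill-taking declines late in the course, mean adherence will be overstated. The therapeutic-response group, meant to hold children with at least 80% adherence over a completed course, could include some below that threshold. An analysis plan written later cannot recover counts that were never made.

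**Working it through.** The Protocol gives no coverage figure to reproduce, so this is direct arithmetic.

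**Inputs.** Course: 60 days (Treatment). Supplies: 60/15 = 4 (Treatment). Counts: 5, weekly (Follow up). Minimum counts: 4 (Data Analysis: three or fewer are excluded). Threshold: 80%, that is 0.80 × 60 = 48 full-dose days. Assumptions: visits run consecutively from treatment start, the daily pill number is constant, and the score uses pill counts alone.

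**Coverage.**
- Five counts: 5 × 7 = 35 days; 35/60 = 58.3%. Uncounted: 25 days (41.7%).
- Four counts with the last one missed: 4 × 7 = 28 days; 28/60 = 46.7%. Uncounted: 32 days (53.3%). If an earlier count is missed instead, the last still falls at day 35 and the 25-day figure applies.
- By day 35 two supplies are finished and the third is 5 days old (35 − 30). The fourth, days 46-60, is not counted at all.
- Weekly counts over the whole course would need 60/7 = 8.57, so 9 visits. A count at the end of each supply (days 15, 30, 45, 60) would need four.

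**Full-course adherence of a child who scores 100%.** The child takes every pill to day 35 and a share x of those after it:

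A = (35 + 25x)/60

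Setting A = 0.80 gives x = (48 − 35)/25 = 0.52.

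| Share x of later pills taken | Full-course adherence | Pill-count score |
|---|---|---|
| 52% | 80.0% | 100% |
| 50% | 79.2% | 100% |
| 40% | 75.0% | 100% |
| 25% | 68.8% | 100% |

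**Sensitivity of the break-even.**
- Coverage of 28 days only: x = (48 − 28)/32 = 62.5%.
- 90% taken in the first 35 days, so the score is 90% and passes the gate: x = (48 − 31.5)/25 = 66%.

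The better the early intake, the larger the late fall that can pass unseen. When early intake only just meets the threshold, even a small late fall takes the child below it.

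**The case against.** **The start day is not given.** This is correct, and the 35 days are inferred. Remaining-pill counts accumulate within a supply, so coverage depends on when the last count falls. Later visits could therefore cover different days. They would cover the whole course only if leftovers were reconciled across supplies, and no such rule is stated.

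**Other records span the course.** The calendar exists to help monitor adherence, and the diary records doses and their timing. The definition's reference to pills provided for each time period could be read as the four 15-day periods. A reader might therefore infer either that late dosing is wholly unrecorded or that it is fully covered. The text supports neither: late doses should appear in these records, but neither record is linked to the percentage, while a minimum number of pill counts is.

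**Completion is required too.** A reader might infer that a child who stops at day 35 scores 100% and enters the response analysis. The Protocol does not support that, because response requires a completed course and those who abandon are excluded from adherence estimates. What survives is partial late under-dosing by a child who stays in treatment. Completion is not defined in a way that would catch it.

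**Direction of bias in response.** A reader might infer that the response result is made too favourable. Nothing in the document shows this. Admitting under-dosed children would more plausibly lower than raise the proportion qPCR-negative at 180 days.

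**Detail left to later documents.** Patient recruitment leaves a monitoring plan to local agreement, and a statistical analysis plan may say how the records combine. That is fair for the combination rule. It does not settle the mismatch, since the schedule, the definition and the gate are all fixed in this Protocol.

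**Conclusion.** The point holds as a mismatch between the pill-count schedule and the course it is meant to measure. As written, up to about 25 of 60 days may go uncounted, or up to 32 if the minimum of four counts is met and the last is the missing one. A child who scores 100% on pill counts can be below 80% over the full course if fewer than 52% of the later pills are taken, for example about 69% when a quarter are taken.

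These figures rest on consecutive weekly visits from treatment start, perfect intake while counts are made (for the 100% score), and scoring on pill counts alone. The Protocol gives no rate of late decline, so the actual overstatement of adherence and the effect on the response proportion are unknown. The change should be made because two primary outcomes depend on the figure and the remedy is cheap.

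**What to change.** Reconcile Treatment, Follow up, and Data Analysis and statistical methods as follows:

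1. Add a count of remaining pills at each 15-day resupply and at the existing day-60 evaluation.
2. Define adherence as pills taken over the whole course divided by pills provided for it. Take physician-directed suspensions and dose reductions, which Follow up allows, out of the denominator so that they are not scored as non-adherence.
3. State how the calendar and the treatment diary are used when a count is missing.
4. Define completion, and apply the 80% gate to the full-course figure.

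If late counts were not made, label the outcome by the period actually measured and do not use it as a full-course gate.

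The cost is a few more counts at contacts that already take place and a revised definition. Reported adherence may be less favourable, and the response group may be smaller.
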